# Audiovisual biofeedback breathing guidance for lung cancer patients receiving radiotherapy: a multi-institutional phase II randomised clinical trial

**DOI:** 10.1186/s12885-015-1483-7

**Published:** 2015-07-18

**Keywords:** Breathing guidance, Motion management, Randomised, Stratified, Phase II clinical trial, Lung cancer, Radiotherapy

## Abstract

**Background:**

There is a clear link between irregular breathing and errors in medical imaging and radiation treatment. The audiovisual biofeedback system is an advanced form of respiratory guidance that has previously demonstrated to facilitate regular patient breathing. The clinical benefits of audiovisual biofeedback will be investigated in an upcoming multi-institutional, randomised, and stratified clinical trial recruiting a total of 75 lung cancer patients undergoing radiation therapy.

**Methods/Design:**

To comprehensively perform a clinical evaluation of the audiovisual biofeedback system, a multi-institutional study will be performed. Our methodological framework will be based on the widely used Technology Acceptance Model, which gives qualitative scales for two specific variables, perceived usefulness and perceived ease of use, which are fundamental determinants for user acceptance. A total of 75 lung cancer patients will be recruited across seven radiation oncology departments across Australia. Patients will be randomised in a 2:1 ratio, with 2/3 of the patients being recruited into the intervention arm and 1/3 in the control arm. 2:1 randomisation is appropriate as within the interventional arm there is a screening procedure where only patients whose breathing is more regular with audiovisual biofeedback will continue to use this system for their imaging and treatment procedures. Patients within the intervention arm whose free breathing is more regular than audiovisual biofeedback in the screen procedure will remain in the intervention arm of the study but their imaging and treatment procedures will be performed without audiovisual biofeedback. Patients will also be stratified by treating institution and for treatment intent (palliative vs. radical) to ensure similar balance in the arms across the sites. Patients and hospital staff operating the audiovisual biofeedback system will complete questionnaires to assess their experience with audiovisual biofeedback. The objectives of this clinical trial is to assess the impact of audiovisual biofeedback on breathing motion, the patient experience and clinical confidence in the system, clinical workflow, treatment margins, and toxicity outcomes.

**Discussion:**

This clinical trial marks an important milestone in breathing guidance studies as it will be the first randomised, controlled trial providing the most comprehensive evaluation of the clinical impact of breathing guidance on cancer radiation therapy to date. This study is powered to determine the impact of AV biofeedback on breathing regularity and medical image quality. Objectives such as determining the indications and contra-indications for the use of AV biofeedback, evaluation of patient experience, radiation toxicity occurrence and severity, and clinician confidence will shed light on the design of future phase III clinical trials.

**Trial registration:**

This trial has been registered with the Australian New Zealand Clinical Trials Registry (ANZCTR), its trial ID is ACTRN12613001177741.

## Background

The precision of radiotherapy can be reduced due to respiratory-related tumour motion, particularly for tumours in the thoracic region, leading to increased irradiation of healthy surrounding tissues, resulting in a significant increase in radiation-related toxicity [1–3]. This is further exacerbated when respiration is irregular in nature (deep/shallow breaths, baseline shifts, suspended breathing, etc.) [4, 5]. A 1Gy increase in tumour dose results in a 4 % improvement in survival, [6] however, a 0.5 cm range of tumour motion can cause a 4 ~ 5 % variation in radiation dose [7] which leads to an increase in mean dose to healthy surrounding tissues resulting in an increase in risk of pneumonitis and radiation toxicity [8, 9].

Techniques such as respiratory gating, breath-holds and tumour tracking are clinically useful for tumour motion management [10, 4, 11]. However, irregular respiration can reduce the efficiency of such motion management techniques, [12, 13] irregular respiration also causes motion artefacts and anatomic errors in medical imaging [14–19].

Breathing guidance is one such technique which specifically aims to produce regular patient breathing by showing the patient how to adjust their breathing in real-time. One such breathing guidance system is the audiovisual (AV) biofeedback system (shown in Fig. 1), developed by Venkat, et al [13].

**Fig. 1 Fig1:**
[figure not shown]
AV biofeedback system (left). Display goggles and real-time position management (RPM) marker block on the abdomen shown. The visual display (right), as seen by the patient, of the AV biofeedback guiding interface shows the waveguide (white curve) and a marker position (grey marker) in real time

AV biofeedback is a real-time, interactive and personalised respiratory guide designed to facilitate regular patient breathing. Table 1 outlines the findings from previous AV biofeedback investigations.

**Table 1 Tab1:** Details of previous AV biofeedback investigations

Investigation author (Year)	Participants	Findings
George [23] (2006)	24 lung cancer patients	• Residual breathing motion within a gating window improved
Venkat [13] (2008)	10 healthy volunteers	• Waveguide breathing guidance produced more regular breathing than bar-model guidance and free breathing
Yang [22] (2012)	Phantom study	• 4D PET image quality improved
An [36] (2013)	Retrospective analysis of George (2006) data	• CTV coverage improved
		• Internal motion variation improved
Kim, [21] Pollock, [37] & Steel [38] (2012–2014)	15 healthy volunteers	• Kim (2012): Breathing regularity of thoracic diaphragm and abdominal wall improved
		• Pollock (2013): Accuracy of kernel density estimation motion prediction improved
		• Steel (2014): Strong correlation between internal and external anatomic motion for both AV biofeedback and free breathing
Lee [24] (2014)	5 healthy volunteers	• Improved 3D MR image quality
		• Reduced gated MRI scan time
Lu [39] (2014)	13 lung & liver cancer patients	• Breathing regularity improved
		• ITV_MIP_ underestimated ITV_10_
Lee [40] (2014)	7 lung cancer patients	• Improved intrafraction lung tumour motion consistency
		• Improved interfraction lung tumour motion consistency

However, none of the studies presented in Table 1 were randomised trials, in addition to this, the findings of a recent literature search yielded that a randomised clinical trial with any breathing guidance intervention has not yet been performed. To fill the gap in the literature, we have designed a multi-institutional, phase II, randomised clinical trial to thoroughly assess the clinical impact of the AV biofeedback breathing guidance system. Based on previous findings, we hypothesise that AV biofeedback will significantly improve breathing regularity and reduce medical imaging errors for lung cancer patients undergoing imaging and treatment procedures during radiotherapy.

This trial has been registered with the Australian New Zealand Clinical Trials Registry (ANZCTR), its trial ID is ACTRN12613001177741.

## Methods/Design

This study aims to assess the clinical impact of AV biofeedback by recruiting 75 lung cancer patients across seven radiation oncology departments. What follows is an outline of the AV biofeedback setup, primary and secondary objectives, participant selection criteria, the study workflow, and statistical considerations for our study design.

### Research Ethics Committee

The protocol for this clinical trial has been reviewed and approved by the Hunter New England Human Research Ethics Committee (HREC). This Human Research Ethics Committee is constituted and operates in accordance with the National Health and Medical Research Council’s ‘National Statement on Ethical Conduct in Human Research (2007)’ (National Statement) and the ‘CPMP/ICH Note of Guidance on Good Clinical Practice’. The Hunter new England HREC has also been accredited by the New South Wales Department of Health as a lead HREC under the single ethical and scientific review. A report on the progress of this clinical trial is required to be submitted annually to the Hunter New England HREC.

### Audiovisual biofeedback system

The AV biofeedback system, as shown in Fig. 1, utilises the Real-time Position Management system (RPM, Varian Medical Systems, Palo Alto, USA) to track the motion of an external marker positioned on the patient’s abdomen. This real-time respiratory-motion is used by the AV biofeedback software to calculate an average cycle of respiration (using a Fourier series fit from 10 obtained respiratory cycles). This average cycle is used as the waveguide (white curve in Fig. 1) which continually moves from right-to-left across the visual display and acts as part of the visual prompt for AV biofeedback. Also on the visual display is a grey marker moving vertically up-and-down corresponding to the anterior-posterior motion of the marker block positioned on the patent’s abdomen. It is the goal for the patient to keep the marker block within inhale-exhale limits (presented as the blue region in Fig. 1) and match the grey marker block over the white waveguide. The audio component of AV biofeedback is classical music playing to the patient; the music fades to silence should the marker block move outside the blue area breathing limits. AV biofeedback has been shown to be compatible in a number of imaging and treatment modalities, [20–22] as well as utilising different types of patient displays [23, 21, 24]. There are two options for patient display in this study: video goggles, or a screen mounted to the couch. Which patient display option is utilised in this study will depend on what is available at each institution.

Figure 2 illustrates the schematic of the AV biofeedback study setup, from the RPM camera monitoring patient breathing motion, to the AV biofeedback computer receiving the RPM signal and extending the AV biofeedback guiding interface to the patient display.

**Fig. 2 Fig2:**
[figure not shown]
Audiovisual biofeedback study setup schematic

### Objectives

This clinical trial will recruit 75 lung cancer patients across 7 radiation oncology departments testing the following objectives:

Primary objective: In a prospective multi-institutional randomised clinical trial we will test the hypothesis that AV biofeedback will significantly improve breathing regularity and reduce medical imaging errors for lung cancer patients undergoing imaging and treatment procedures during radiotherapy.

Secondary objectives will involve patient-specific and department-specific objectives:

Patient-specific objectives are to evaluate the impact of AV biofeedback by:Quantifying the proportion of patients for whom breathing is more regular with AV biofeedback,Quantifying the variability in breathing motion throughout a course of treatment,Quantifying the improvement in image quality with AV biofeedback,Evaluating the patient experience through a perception of care survey,Developing indications and contra-indications for the use of AV biofeedback,Quantifying the differences in image-guided radiotherapy (IGRT) shifts during treatment, andRecording toxicity outcomes for up to 12 months after treatment has been completed.

Department-specific objectives are to evaluate the impact of AV biofeedback on clinical testing by:Quantifying any practice changes (e.g. margin reduction),Quantifying the impact on workflow using the AV biofeedback device through time-motion studies,Evaluating the operator and clinician confidence in the AV biofeedback device’s reliability and clinical efficacy through a technology-impact survey,Quantifying the system robustness through hardware and software fault reporting, andPerforming system quality assurance, sharing the results through web-based uploads and provide feedback for QA improvement.Our methodological framework will be based on the widely used Technology Acceptance Model (TAM) [25, 26]. The TAM gives qualitative scales for two specific variables, perceived usefulness and perceived ease of use, which are fundamental determinants for user acceptance.

### Study participant selection criteria

This study will recruit patients with cancer of the lung receiving external beam radiation therapy. Patients fitting the eligibility criteria (see below) will be identified and introduced to this study by their treating physicians, who will participate as investigators in this study. The eligibility criteria are as follows:Lung cancer patientsi.No restrictions to type of external beam radiation therapy being receivedii.Primary or secondary cancer>18 years oldNo gender or ethnic restrictionsAn ECOG score in the range of 0 to 2Able to give written informed consent and willingness to participate and comply with the studyNo pregnant / lactating woman

### Study workflow

Once informed consent has been obtained, the patient will be randomised into either the intervention or control arm of the study. For patients randomised into the intervention arm, prior to their planning and treatment they will undergo a breathing decision session during which they will breathe both with and without the guidance of AV biofeedback. Preceding each breathing session will be a training session to familiarise the patient with the AV biofeedback system. After the breathing decision session has been completed, the most reproducible breathing condition (AV biofeedback or free breathing) will be determined in situ by an ‘Analyse Respiratory Session’ function within the AV biofeedback software. It will be the most reproducible breathing condition that will continue to be used throughout the rest of that particular patient’s planning and treatment. The flowchart for this study is shown in Fig. 3.

**Fig. 3 Fig3:**
[figure not shown]
Study flowchart

For all patients, each follow-up visitation they have with their treating physician for the first 12 months after their treatment has finished, their treating physician will complete a toxicity report to satisfy the Secondary Patient-Specific Objective 7: Recording toxicity outcomes for up to 12 months after treatment has been completed by reporting the occurrence and severity of any radiation toxicities.

### Patient randomisation

This trial is stratified, hence, study group random allocation will be determined by minimisation [27, 28]. Patients will be stratified by treating institution and for treatment intent (palliative vs. radical) and minimisation considerably reduces the imbalance of these stratification factors across the control and intervention groups of the study. Patients will be randomised in a 2:1 ratio, 2 out of 3 patients will be randomised into the AV biofeedback (intervention) arm and 1 out of 3 will be randomised into the free breathing (control) arm as illustrated by Fig. 3.

### Sample size and power calculation

The statistical considerations for this study are largely based on a previous study conducted at Virginia Commonwealth University (VCU) on 24 lung cancer patients [23, 29]. Prior to this multi-institutional clinical trial, the VCU study was the largest AV biofeedback investigation, recruiting a total of 26 lung cancer patients, however, 2 patients dropped out due to not being treated with radiotherapy or rapid worsening of disease, and so their data was not collected. In the VCU study 109 breathing sessions were performed comparing AV biofeedback to free breathing, of which, 87 sessions (80 %) demonstrated more regular breathing with AV biofeedback. Framing this is in a more clinical relevant way: irregular breathing motion exacerbates the systematic errors (Σ) arising from motion image artefacts and variations between the planned and treated anatomy, as well as random errors (σ) from day-to-day variations in the treated anatomy [30, 15, 31]. To combine systematic and random errors and estimate the margin contribution due to breathing irregularity we will use the van Herk method [32]: margin = 2.5Σ + 0.7σ, incorporating the respiratory components of systematic and random errors. A clinically significant difference in clinical improvement due to AV biofeedback has been determined to be a margin calculation of less than 5 mm. This magnitude of reduction was elected as clinically significant because this is the same magnitude of displacement attributed to contributing to significant artefacts and errors during radiotherapy procedures as detailed in AAPM Task Group 76 [4]. From this van Herk calculation, in the VCU study there were 14/24 patients with margins <5 mm with AV biofeedback, while only 5/24 for free breathing.

In this proposed study, to get a more accurate indication of the proportion of patients with reduced margins calculated using the van Herk method we have designed an exploratory phase II randomised study examining the potential impact of an AV biofeedback system in regulating breathing in patients receiving radiation therapy for the treatment of lung cancer. Without the AV biofeedback system, it is conservatively estimated that approximately 40 % of patients naturally exhibit regular breathing (margin component below 5 mm). Increasing this proportion to 60 % using the AV biofeedback system would be clinically worthwhile. Based on Simon’s design, [33] a sample size of 50 patients receiving the AV biofeedback system will have at least 80 % power with 95 % confidence to rule out a regular rate of 40 % in favour of a 60 % rate. To minimise patient selection bias and provide an estimate of regular breathing from a contemporary control, the proposed design will be a randomised phase II with a 50 patients receiving the intervention and 25 receiving current standard of care. Patients will be randomised in a 2:1 ratio, with 2/3 of the patients being recruited into the AV biofeedback (intervention) arm and 1/3 in the free breathing (control) arm as illustrated by Fig. 3. 2:1 randomisation is appropriate as within the interventional arm there is a screening procedure where only patients whose breathing is more regular with AV biofeedback use this system for their imaging and treatment procedures. Patients will be stratified by treating institution and for treatment intent (palliative vs. radical) to ensure similar balance in the arms across the sites. As the study is not powered for formal comparisons between the groups, estimates of the proportion of patients which do not experience irregular breathing will provide information as to whether further investigation is warranted.

Assuming a contamination and dropout rate of no more than 10 %, this study will require that 75 + 8 = 83 patients be recruited (the 10 % value was based on the 2/26 patient drop-out rate in the VCU study).

Patients at each institution will be treated per department protocol with no additional constraints on dose, fractionation, immobilisation or image guided procedures. Results will be adjusted for institution (using a fixed effect) to account for differences between institutions.

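### The stated power is for 50 patients receiving AV biofeedback, but 50 is the randomised arm, some of whom will not receive it; at least 80% is assured only if the 60% target covers the whole arm

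*Protocol article*

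**What the plan says.** All quotes are from the Protocol article.

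- **Sample size and power calculation, planning rates.** Without the system, "approximately 40 % of patients naturally exhibit regular breathing (margin component below 5 mm"). The target follows: "Increasing this proportion to 60 % using the AV biofeedback system would be clinically worthwhile".
- **Same section, power.** The design is a single-arm test of Simon's type, with the stated aim of "80 % power with 95 % confidence to rule out a regular rate of 40 % in favour of a 60 % rate". The number behind it counts patients who are given the system: "a sample size of 50 patients receiving the AV biofeedback system will have at least" that power. The 50 then becomes the intervention arm of a 75-patient trial allocated 2:1.
- **Same section, screening.** The 2:1 ratio is justified by a step within that arm, under which "only patients whose breathing is more regular with AV biofeedback use this system for their imaging and treatment procedures".
- **Study workflow.** The decision session comes after randomisation and before planning. It fixes AV biofeedback or free breathing for the rest of that patient's course.
- **Abstract, Methods/Design.** Patients who breathe more regularly without the system "will remain in the intervention arm of the study but their imaging and treatment procedures will be performed without audiovisual biofeedback".
- **Allowance.** Recruitment rises from 75 to 83 for contamination and dropout of up to 10%. The only basis given is 2/26 drop-outs in the earlier study, which were due to not being treated with radiotherapy or to rapid worsening of disease.
- **Earlier study.** "In the VCU study 109 breathing sessions were performed comparing AV biofeedback to free breathing"; 87 of the 109 (80%) were more regular with AV biofeedback.

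**The concern.** The unit in the power statement is a patient who receives AV biofeedback. The unit in the design is a patient randomised to an arm in which the software decides who receives it. The two counts agree only if nobody is screened off, and the protocol expects some to be.

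The text does not say whether 60% is the rate hoped for among users or across the whole arm, and the answer changes both the power and the meaning of the result. If the whole arm is tested and 60% belongs to users, non-users with a lower rate dilute it. If only users are tested, the sample shrinks. The group tested has then been chosen after randomisation for responding well, while the 40% null describes unselected patients. That works against the protocol's own aim of limiting patient selection bias.

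The protocol says the study is not powered for formal comparisons between groups, so this is its only power calculation.

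**Working it through.** **Inputs.** From Sample size and power calculation: null rate 0.40, target rate 0.60, n = 50, 95% confidence, power at least 80%, and 87/109 sessions better with AV biofeedback. Sidedness is not stated; one-sided 0.05 is used here because it reproduces the claim. Two inputs are assumptions, since the protocol gives neither: the proportion of *patients* screened off and the regular-breathing rate in those patients.

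**Step 1: reproduce the plan's figure.** Take the smallest cut r with P(X ≥ r | n = 50, p = 0.40) ≤ 0.05.
- r = 26 gives 0.057, which is too large; r = 27 gives 0.031.
- Power = P(X ≥ 27 | 50, 0.60) = 0.844.

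So the claim of at least 80% is correct for 50 patients whose rate is 60%.

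**Step 2: how many would use the system.** Applying the session proportion to patients as an approximation, 50 × 87/109 = 39.9, or about 40 users and 10 non-users (22/109 = 20%).

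**Step 3: whole arm analysed, 60% among users only.** Arm rate = (1 − q) × 0.60 + q × p_non, where q is the proportion screened off and p_non the non-user rate. Power = P(X ≥ 27 | 50, arm rate).

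| q | p_non | Arm rate | Power |
|---|---|---|---|
| 20% | 0.40 | 0.8 × 0.60 + 0.2 × 0.40 = 0.56 | 66.7% |
| 20% | 0.50 | 0.8 × 0.60 + 0.2 × 0.50 = 0.58 | 76.4% |
| 20% | 0.60 | 0.60 | 84.4% |
| 10% | 0.40 | 0.9 × 0.60 + 0.1 × 0.40 = 0.58 | 76.4% |
| 30% | 0.40 | 0.7 × 0.60 + 0.3 × 0.40 = 0.54 | 55.8% |

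Break-even: 80% power needs an arm rate of about 0.588. At q = 20% that means p_non = (0.588 − 0.48)/0.2, or about 0.54.

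**Step 4: users only, at 60%.**
- Exactly 40 users: cut 22, alpha 0.039, power 79.1%.
- Number of users varying as Binomial(50, 0.8), cut reset for each number: average power 76.8%.
- All 83 recruited and none lost: 83 × 2/3 × 87/109 = 44.2; with 44 users the cut is 24 and power 81.4%.

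**Step 5: does the 10% allowance cover screening?** It adds 8 patients, and its stated basis is 2/26 = 7.7% drop-out. Screening is a separate loss of users with no allowance of its own.

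**The case against.** The strongest reply is that 60% was always a target for the whole arm. The sentence that sets it speaks of raising a proportion of patients and calls that rise worthwhile; it does not predict a rate among selected users. The nearest figure from the earlier study, 14/24 (58%) with AV biofeedback, comes from a study for which the article describes no screening step. It therefore appears to include poor responders already, and diluting it again would count them twice. The decision session also gives each patient the more reproducible condition, so the strategy should do no worse than guidance for everyone. Non-users, being chosen because they breathed more regularly unaided, may well exceed 40%.

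Most of this stands. A reader might infer that the trial falls short of 80% power whichever way it is analysed. The documents do not support that: under the whole-arm reading power is 84%. The 67% figure needs a 40% rate in non-users, which the protocol does not give for them. Nor can it be taken as fact that a fifth of patients will be screened off, since 80% is a share of sessions. The loss from head count alone is about one point below 80% at 40 users. If users are favourably selected, their rate could exceed 60%, so the main fault of a users-only test is bias against the null, not lost power.

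A reader might also infer that the 2:1 rationale makes sense only if non-users leave the analysis. That does not follow: more patients on the system also serves the objectives on patient experience, indications, workflow and fault reporting.

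The reply does not remove the mismatch. The power sentence says receiving, the design says randomised, and nothing in the text states the whole-arm reading. This is a conflict between the protocol's own statements, not a detail left to an analysis plan.

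**Conclusion.** The point holds as a mismatch between the stated basis of the power and the design. The calculation itself is correct for 50 patients at a 60% rate. The claim of at least 80% carries over to the trial described if 60% is the target for everyone randomised to the intervention arm (84%).

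If 60% applies to users only, whole-arm power at 20% screened off is about 67% to 76% for non-user rates of 40% to 50%. With non-users at 40%, it is 56% to 76% for 30% down to 10% screened off. A users-only test has about 77% to 79% power and a selected comparison. These figures rest on an exact one-sided 0.05 test, on the session proportion standing in for a patient proportion, and on non-user rates that the protocol does not give.

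The study is exploratory and the remedy is wording, so this is a should-fix matter.

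**What to change.** 1. In Sample size and power calculation, replace 50 patients receiving AV biofeedback with 50 patients randomised to the AV biofeedback strategy.
2. Name all patients randomised to that arm as the primary analysis set, whichever breathing condition the decision session assigns.
3. Either state that 60% is the target for that whole arm, non-users included, so that 84% stands; or restate the power as a range under an explicit patient-level screening rate and non-user rate.
4. Report users-only results descriptively, without a test against the 40% null, because users are selected after randomisation on favourable response.

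The cost is a few sentences and possibly a less favourable stated power. No extra patients are needed, and the 2:1 allocation can stay as it is.

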## Discussion

This clinical trial marks an important milestone in breathing guidance studies as it will be the first randomised, controlled trial providing the most comprehensive evaluation of the clinical impact of breathing guidance on cancer radiation therapy to date. Based on the structure of previous investigations, and taking into consideration the increase in scope of this study, the authors have designed a multi-institutional, randomised, phase II, stratified clinical trial to test the hypothesis that audiovisual biofeedback breathing guidance will significantly improve breathing regularity and reduce medical imaging errors for lung cancer patients undergoing imaging and treatment procedures during radiotherapy. While patients will be stratified by treating institution and for treatment intent, the study is not powered for formal comparisons between the these stratified groups; estimates from the current proposed study of the proportion of patients which do not experience irregular breathing will provide information as to whether further investigation is warranted. Further to this, objectives such as determining the indications and contra-indications for the use of audiovisual biofeedback, evaluation of patient experience, radiation toxicity occurrence and severity, and clinician confidence will shed light on the design of future phase III clinical trials.

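### The abstract calls the trial powered for breathing regularity and image quality, but the only sizing shown is a one-arm test of a different endpoint, and the text is inconsistent on which comparisons are unpowered

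*Protocol article*

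**What the plan says.** Four parts of the protocol article bear on what the trial is sized to show.

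- **Abstract, Discussion paragraph:** "This study is powered to determine the impact of AV biofeedback on breathing regularity and medical image quality".
- **Objectives:** the primary objective, set in a randomised trial, is that "we will test the hypothesis that AV biofeedback will significantly improve breathing regularity and reduce medical imaging errors". The Background and the closing Discussion repeat the hypothesis.
- **Sample size and power calculation:** a 40% rate of regular breathing, defined as a margin component below 5 mm, is assumed without the device. On the target, "Increasing this proportion to 60 % using the AV biofeedback system would be clinically worthwhile". Fifty patients on the device are said to give "at least 80 % power with 95 % confidence to rule out a regular rate of 40" per cent, citing Simon's design. The 25 controls are there to limit selection bias and provide a contemporary estimate. The section calls the study exploratory and adds: "As the study is not powered for formal comparisons between the groups".
- **Discussion:** the caveat returns with a different object: "the study is not powered for formal comparisons between the these stratified groups". The strata are treating institution and treatment intent.

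The Data analysis section names the metrics for the primary objective: RMSE in displacement and in period for regularity, and the NCC artefact method for 4D-CT image quality. The proportion with margin below 5 mm is not among them.

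**The concern.** The abstract claims a property that the sample size section does not give the design. A one-arm test against a fixed 40% says whether the intervention arm exceeds an assumed rate. It does not test the randomised contrast, it does not use RMSE, and it says nothing about image quality.

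Two misreadings could follow. If the arms are compared and the result is not significant, a reader relying on the abstract could take it as a negative result from a powered trial. If the intervention arm beats 40%, that could be reported as confirming the randomised hypothesis, which it does not test. The changed caveat in the Discussion makes both easier, because a reader of that section alone would think that only comparisons between strata lack power.

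**Working it through.** **Inputs**, all from Sample size and power calculation: 50 intervention and 25 control patients (75 evaluable; 83 are to be recruited to allow for loss); rates 40% and 60%; at least 80% power; 95% confidence. Whether the test is one- or two-sided is not stated, so both are shown.

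**1. The plan's own figure.** Exact binomial, n = 50. The smallest cut-off with one-sided error at most 0.05 is 27: P(X ≥ 27 | 0.40) = 0.031 and P(X ≥ 27 | 0.60) = 0.844. The normal approximation gives 89.3% power one-sided and 82.3% two-sided. So at least 80% with 50 patients reproduces as a one-arm test. At one-sided 0.025 the exact cut-off is 28 and power is 76.6%, so under the exact method the claim needs a one-sided 5% test.

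**2. The same rates compared between arms.**

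- Pooled rate = (25 × 0.40 + 50 × 0.60)/75 = 0.533.
- SE under the null = √(0.533 × 0.467 × (1/25 + 1/50)) = 0.1222.
- SE under the alternative = √(0.24/25 + 0.24/50) = √0.0144 = 0.12.
- Two-sided 5%: power = Φ((0.20 − 1.96 × 0.1222)/0.12) = Φ(−0.33) = 37.1%.
- One-sided 5%: power = Φ((0.20 − 1.645 × 0.1222)/0.12) = Φ(−0.01) = 49.7%.

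| Method | Two-sided 5% | One-sided 5% |
|---|---|---|
| Pooled normal | 37.1% | 49.7% |
| Unpooled normal | 38.5% | 50.9% |
| Arcsine | 37.6% | 50.0% |
| Chi-square, exact enumeration | 40.5% | 49.7% |
| Fisher exact | 34.2% | 40.5% |
| Continuity-corrected | 28.1% | 39.8% |

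Every variant lies between 28% and 51%.

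**3. Precision.** The half-width of the 95% confidence interval is 1.96 × 0.12 = 0.235, about ±24 points. An observed difference of exactly 20 points would have an interval from about −4 to +44 points.

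**4. Size needed for 80% between-arm power at 2:1, two-sided 5%.** Control n = (1.96 × √(0.2489 × 1.5) + 0.8416 × √(0.24 × 1.5))² / 0.20² = (1.198 + 0.505)²/0.04 = 72.5, rounded up to 73. With 146 in the intervention arm the total is 219. One-sided 5% gives 58 + 116 = 174.

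**5. The metrics named for the primary objective.** No SD or effect size is shown for RMSE or NCC, so their power cannot be computed. For any continuous outcome analysed as a difference in means, the effect detectable with 80% power, two-sided 5%, is (1.96 + 0.8416) × √(1/25 + 1/50) = 2.80 × 0.245 = 0.69 SD. The article does not show whether a difference of that size is plausible or worthwhile.

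**6. Sensitivity to the rates.** The earlier 24-patient study cited in the same section had 5/24 (20.8%) with margins below 5 mm on free breathing and 14/24 (58.3%) with the device. Entering those rates at 25 versus 50 gives about 88-91% two-sided power.

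**The case against.** The strongest case on the other side has five parts.

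- **The figure is for a different endpoint.** A reader might infer that the trial's actual power for its primary objective is 37-41%. The article does not support that. The figure belongs to the margin proportion, while Data analysis assigns RMSE and NCC to the primary objective, and their power is unknown. This stands.
- **The figure depends on assumptions.** The test's sidedness is not stated, the 40% rate is described as conservative, and the earlier study's rates would give about 90% power. This stands as a qualification. But 40% and 60% are the design rates the protocol chose, so they are the fair basis for a conditional figure.
- **The word groups may mean strata.** In the sample size section the caveat directly follows the sentence on stratification, and the Discussion says stratified groups outright. Against this, the rest of the sentence concerns the proportion without irregular breathing, and Patient randomisation uses groups for the control and intervention arms. Arms is the more natural reading, but it is not settled. A reader might infer that the Discussion conceals the limitation; the text shows only inconsistency. Reading groups as strata does not rescue the abstract, because the sizing shown is still one-arm.
- **No between-arm test is named.** It is inferred from the randomised hypothesis of significant improvement. The inference is reasonable, but it is an inference.
- **The study is labelled exploratory, and the article is condensed.** The label lessens the harm for anyone who reads the sample size section. It does not correct the abstract. For image quality one can say only that no calculation is shown, not that none exists.

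**Conclusion.** The concern holds in this form: the abstract claims power for breathing regularity and image quality, and the article shows sizing only for a one-arm test of the margin proportion against 40%. That one-arm calculation is sound at one-sided 5%; the fault lies in what it is said to support.

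For the margin endpoint only, at 40% versus 60% with 25 versus 50 patients, between-arm power is about 37-41% if two-sided 5% is assumed and about 41-50% if one-sided 5%. Fisher's test and the continuity correction give less. On the two-sided figures, a trial in which the device delivers exactly the stated worthwhile effect would miss significance between the arms about 59-63% of the time. For RMSE and NCC no power can be stated, only that about 0.7 SD would be detectable. The conclusion that the passages conflict does not depend on sidedness or on how groups is read.

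**What to change.** 1. In the abstract, withdraw the power claim or limit it to the one-arm test of the proportion with margin component below 5 mm against 40%.
2. Reconcile Objectives, Sample size and power calculation, and Data analysis together. Name that proportion as the sized endpoint. Keep the RMSE and NCC comparisons, and so the imaging-error half of the objective, but label them and the between-arm difference as unpowered estimates reported with 95% confidence intervals. Changing the objective alone would leave Data analysis naming other metrics and would drop image errors without saying so.
3. State the conditional between-arm power with its assumptions: margin endpoint, 40% versus 60%, 25 versus 50 patients, and the sidedness chosen.
4. Make the caveat in the sample size section and in the Discussion say explicitly that it covers the randomised arms as well as the institution and intent strata.

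No patients are added. The cost is a less favourable stated claim. Sizing for the between-arm test instead would take about 219 evaluable patients (two-sided 5%, 80% power, 2:1).
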